### Planned Statistical Analysis for Pain Outcomes

The following parameters will be measured and statistically compared between baseline (energy storing and returning condition) and each follow-up visit with the powered ankle-foot prosthesis (weeks 4 and 8):

Joint reaction forces on the lower back (L5 and S1) and contralateral (intact) kneesPEQ pain scoresFunctional outcome measures (6MWT, AMPpro, and CHAMP)

Spearman correlations will be calculated to correlate data between pain and lower extremity kinematic and kinetic parameters of interest and pain and functional outcome values across the groups. Linear mixed-effects models will be used to identify statistically significant differences in pain scores and biomechanical variables listed in the previous section for all walking speeds. For example, a linear mixed-effects regression will be used to examine the relationship between peak reaction moments at L5 and S1 and pain for each prosthetic ankle-foot condition. Pair-wise comparisons will be tested for significance using linear contrasts with a Tukey honestly significant difference or by applying a Bonferroni correction, where applicable.

Multiple linear regression will be performed with PEQ pain as the dependent variable. Because of the large number of predictor variables in relation to the number of participants, penalized methods (eg, ridge regression or lasso) will be used to identify variables that contribute the most to the prediction model. Penalized methods add a tuning parameter to the regression model that shrinks the less important coefficients toward 0. Cross-validation will be used to select the best tuning parameter value [62]. The independent variables will be comprised of functional parameters (eg, peak joint reaction forces) and the condition (ankle-foot type and intervention).

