#### Baseline Data Capture

Regardless of the group assignment, all participants will undergo baseline data capture using their current passive energy storing and returning prosthesis. The study prosthetist will ensure proper fit and alignment of the prosthesis before any data collection. Once fit and alignment are confirmed, the participants will complete 3 surveys: an assessment of quality of life, the Prosthesis Evaluation Questionnaire (PEQ), and the PEQ Addendum. Then, pain, cognitive load, neurocognition, biomechanical gait analysis, and functional outcomes will be captured at baseline for all participants on their current passive energy storing and returning prosthesis.

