### Planned Statistical Analysis for Biomechanical and Functional Outcomes

Although there are numerous biomechanical and physiological parameters that can be evaluated following gait analysis [61], this investigation will focus on the biomechanical parameters that are most relevant, commonly used, able to discriminate, and have specific clinical relevance for individuals with transfemoral limb loss. The primary biomechanical outcome measures will include measures of rollover shape, individual characteristics of the 3D ground reaction force, and ankle, knee, and hip joint angles, moments, and powers (on both the intact and affected limbs). To evaluate the load distribution of the medial and lateral knee compartments, the peak resultant ground reaction force, ground reaction force rate, peak knee external adduction moments, and knee external adduction moment rate will be compared between the baseline (passive energy storing and returning condition) and the powered condition at each follow-up visit.

Linear mixed-effects models will be used to identify statistically significant differences in gait temporal-spatial and biomechanical variables for all walking speeds. The fixed effects will be the average differences in gait biomechanical and temporal-spatial variables by prosthetic ankle type (powered vs passive). These models also estimate random effects because of differences in mean biomechanical variables across participants, as well as the random effects associated with minimized variability, as the participants will be tested with both prostheses. For example, a linear mixed-effects regression will be used to examine the relationship between the intact knee peak external adduction moment and the prosthetic ankle-foot condition. Peak intact knee external adduction moment will be the dependent variable, whereas ankle-foot condition will be the independent variable, and participant-by-ankle-foot condition will be modeled as random effects. Pair-wise comparisons will be tested for significance using linear contrasts with a Tukey honestly significant difference or by applying a Bonferroni correction, where applicable. In addition, linear mixed-effects regression will be used to determine the association between prosthetic peak ankle power and foot condition.

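### The penalised PEQ-pain regression needs repeated rows per participant but is specified with no participant effect and no participant-level cross-validation folds

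*Protocol article*

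**What the plan says.** In Planned Statistical Analysis for Pain Outcomes, the protocol article first plans correlations and linear mixed-effects models for pain, and then a separate prediction model: "Multiple linear regression will be performed with PEQ pain as the dependent variable". The reason given for shrinkage is "Because of the large number of predictor variables in relation to the number of participants", and the tool is that "penalized methods (eg, ridge regression or lasso) will be used to identify variables that contribute the most to the prediction model". On tuning, the text says only "Cross-validation will be used to select the best tuning parameter value". The predictor list is: "The independent variables will be comprised of functional parameters (eg, peak joint reaction forces) and the condition (ankle-foot type and intervention").

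The design fixes who is measured on which device. Under Baseline Data Capture, "all participants will undergo baseline data capture using their current passive energy storing and returning prosthesis". The pain section then compares baseline with "each follow-up visit with the powered ankle-foot prosthesis (weeks 4 and 8").

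For the gait outcomes, Planned Statistical Analysis for Biomechanical and Functional Outcomes uses random effects and gives the reason "as the participants will be tested with both prostheses". The cognitive section also treats participants as random. The PEQ-pain regression names no participant term, and the article does not state the unit from which folds are drawn.

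**The concern.** Ankle-foot type is the same for everyone at any one visit, so its coefficient can be estimated only by entering several visits of the same people. Those rows are correlated. Multiple linear regression, penalised or not, has no term for that correlation.

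Cross-validation is affected as well. If one visit of a participant is held out while another stays in the training set, stable gait and function variables can act as a label for the person, and the person's usual pain level is then partly predicted from that label. The held-out error looks better than it would in new people, so the selected penalty is too weak. The stated purpose is to find the variables that matter most for predicting pain, and that list could then include variables with no relation to pain.

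**Working it through.** The plan gives no figure for this regression, so there is none to reproduce. The check has three parts.

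**1. Does the stated model force repeated rows?**

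Inputs: 30 participants and three visits (Power Analysis and Sample Size Estimation); passive device at baseline, powered at weeks 4 and 8. Code passive as 0 and powered as 1.

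- Three rows per person: the values are 0, 1, 1, and every participant's mean is 2/3. The variance between participants is 0. The variance within participants is (2/3) x (1/3) = 2/9.
- Two rows per person (baseline and one follow-up): every mean is 1/2. Between is 0, within is 1/4.
- One row per person at a common visit: the variable is constant and its coefficient cannot be estimated.

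The model therefore uses 30 x 2 = 60 to 30 x 3 = 90 rows from 30 people.

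**2. How often would row-level folds split a participant?**

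Assume 10 folds (the article gives no number).

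- 90 rows, 9 per fold: both other rows of the same person share the held-out row's fold with probability (8/89) x (7/88) = 56/7832 = 0.007. At least one is in the training set with probability 0.993.
- 60 rows, 6 per fold: the other row is in the training set with probability 1 - 5/59 = 0.915.

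Under row folds, nearly every held-out row has a sibling in the training data.

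**3. What does that do to the lasso?**

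Simulation with no true association. For participant i and visit j, each predictor is x = sqrt(ICCx) u_i + sqrt(1 - ICCx) e_ij. Pain is built the same way with ICCy, independently of every predictor. Lasso used 10 folds, 25 penalties from the smallest that empties the model down to 1/100 of it, and the minimum cross-validated error. The intraclass correlations (ICC) and the predictor counts (20 and 40) are assumptions.

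Three rows per participant, 60 data sets per line. R2 is the reduction in cross-validated error relative to the largest penalty. The last column evaluates the penalty chosen by row folds on participant folds.

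| Predictors | ICCx / ICCy | Mean kept, row folds | Mean kept, participant folds | Any kept, row / participant | R2, row folds | R2, same penalty, participant folds |
|---|---|---|---|---|---|---|
| 20 | 0 / 0 | 1.6 | 1.6 | 47% / 42% | 0.01 | 0.01 |
| 20 | 0.5 / 0.5 | 4.3 | 1.4 | 75% / 42% | 0.05 | -0.01 |
| 20 | 0.7 / 0.7 | 9.0 | 2.8 | 85% / 47% | 0.13 | -0.06 |
| 20 | 0.9 / 0.7 | 12.5 | 1.6 | 98% / 37% | 0.20 | -0.29 |
| 40 | 0 / 0 | 2.5 | 2.9 | 43% / 43% | 0.02 | 0.01 |
| 40 | 0.5 / 0.5 | 9.2 | 3.4 | 72% / 45% | 0.07 | -0.02 |
| 40 | 0.7 / 0.7 | 18.9 | 3.2 | 97% / 48% | 0.20 | -0.20 |
| 40 | 0.9 / 0.7 | 24.9 | 4.3 | 100% / 57% | 0.34 | -0.50 |

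Two rows per participant, 80 data sets, mean kept with row v participant folds:

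- ICC 0.5: 3.2 v 2.1 of 20, and 5.8 v 3.3 of 40.
- ICC 0.7: 5.8 v 1.7 of 20, and 12.9 v 3.7 of 40.

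One row per participant, 100 data sets: 2.2 and 2.0 of 20, and 3.5 and 3.1 of 40. Here the two fold rules are the same procedure, so these differences show the size of the simulation noise.

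At ICC 0.7 with three rows, the excess due to row folds is 9.0 - 2.8 = 6.2 of 20 and 18.9 - 3.2 = 15.7 of 40.

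**The case against.** The strongest reply is that the article does not state how folds are drawn. Grouped folds are compatible with every word of it, and fold construction is the kind of detail that a full protocol or analysis plan would hold. The authors also justify shrinkage by the number of participants rather than of observations, and they use participant random effects elsewhere. A reader might infer from the text that rows will be treated as independent and folds drawn by row. The documents do not support that inference. It is a risk left open, not a stated choice.

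Other parts of the reply also stand:

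- The counts of predictors kept apply to lasso only. Ridge, the other named example, sets no coefficient to zero, although its penalty would be tuned on the same folds.
- The article plans cross-validation for tuning and does not plan to report a cross-validated R2. It would be too strong to say that the plan will publish inflated accuracy.
- Not all noise selection comes from the folds. With participant folds, at least one noise predictor was still kept in 37% to 57% of data sets with ICC above 0, much the same as with one row per person (46% to 52%).
- The main device and pain comparisons use mixed models. This regression is supplementary and plays no part in the sample size.

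The reply does not reach the model itself. The article states both the method and the predictor list, and together they require repeated rows for which that method has no term. The same section uses mixed models for pain just before it turns to this regression.

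**Conclusion.** The point holds in a limited form. As specified, the PEQ-pain regression must use two or three correlated rows per participant, and it has neither a participant effect nor a stated rule that keeps those rows in one fold. That much follows from the design and the predictor list without any assumption.

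The size of the harm is conditional. It needs row-level folds, appreciable within-person correlation in both pain and the predictors, and the lasso option. Under those conditions, with an assumed ICC of 0.7 and three rows each, lasso keeps about 9 rather than 3 noise predictors of 20. With two rows it keeps about 6 rather than 2. At ICC 0 there is no excess. Substantial correlation is plausible for the same people measured over 8 weeks, but the article gives no value. The change is worth making; it does not threaten the trial's main comparisons.

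**What to change.** In Planned Statistical Analysis for Pain Outcomes, state three things:

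1. All rows of a participant stay in the same cross-validation fold.
2. The penalised model includes a participant random intercept, in line with the mixed models used elsewhere in the article.
3. If predictive accuracy is reported, it is the participant-level cross-validated value.

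The first item removes the excess selection shown above. The second addresses the correlated errors; it was not simulated here, and it does not replace the first. Reducing the data to one within-person change score per participant would not serve, because everyone moves from passive to powered and ankle-foot type would no longer be estimable as a predictor.

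The cost is a short addition to the text, a grouping option for the folds, and somewhat more analysis work for a penalised model with a random intercept. Apparent predictors will probably be fewer or weaker. The sample size and data collection do not change.

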### Planned Statistical Analysis for Cognitive Load and Neurocognitive Outcomes

Linear mixed-effects models will be performed to examine the differences between the ankle-foot devices on cognitive performance, walking speed, and subjective responses to attention. The parameters in the linear effects model will include prosthetic ankle-foot type, PT intervention, and participants. Ankle-foot type, PT intervention, and cognitive performance will be treated as fixed effects, whereas participants will be treated as random. The total number of errors and the error rates for the cognitive task will be calculated, and the mean error rate will be determined for each cognitive task performed by each participant. Repeated-measures ANOVA will be used to compare the error rates for the 3 cognitive tasks. Fisher least significant difference test will be used to make post hoc comparisons.

For the neurocognitive battery, Pearson correlation coefficients (pair-wise 2-tailed) will be calculated for all variables of interest. Stepwise multiple regression will be performed with the neurocognitive scores (Neurocognitive Index, composite memory, cognitive flexibility, and complex attention scores) as the dependent variable. The independent variables will comprise functional outcomes, pain, and gait biomechanics, including asymmetry index.

### Power Analysis and Sample Size Estimation

The sample size was based on a power analysis of 3 biomechanical measures (leading limb work, ground reaction force rate, and knee adduction moment rate) and 1 functional outcome (6MWT distance), and 1 subjective outcome (PEQ—utility) obtained from preliminary analyses, with all measurements obtained at baseline and 2 additional measurements over an 8-week period. The sample size was calculated for the group-by-time interaction, which tests the differences in change over time between the study groups. Assuming an α error rate of 5%, Table 5 presents the power achieved for each measurement for 30 participants, 15 (50%) in each group.

**Table 5 table5:** Power analysis and sample size estimation.

Measure	Difference, mean (SD)	Power (N=30)
Leading limb work (J/kg)	0.03 (0.04)	85
Ground reaction force rate (N/kg/s)	15 (26.9)	82
Knee adduction moment rate (N m/kg/s)	1.1 (1.2)	98
6MWT^a^ distance (m)	60 (61)	96
PEQ^b^—utility	8.4 (8.8)	96

^a^6MWT: 6-minute walk test.

^b^PEQ: Prosthesis Evaluation Questionnaire.

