### Limitations

This investigation will not address the varied dosing, timing, frequency, and duration of the device-specific rehabilitation protocol. However, the frequency of PT visits and protocol timing will be evaluated for each participant, which can provide preliminary data for a future study to optimize the rehabilitation strategy. The heterogeneity of the sample population may also limit the generalizability of the outcomes to a more diverse population. In addition, the statistical analysis models will also adjust for specific parameters (eg, age, time since limb loss, and etiology of limb loss), which may limit the sample size and interpretability of the results. The type of microprocessor knee used by each participant will not be prescribed and may be a confounding factor. This influence of the microprocessor knee type will be evaluated in the statistical models. Finally, a 4-week assessment following completion of the device-specific protocol may not be sufficient to evaluate any PT rebound effects or long-term changes in gait, specifically regarding the effectiveness of the acute PT intervention on gait biomechanics.

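### The only randomised contrast the article defines is a difference in change from baseline; stating a baseline-adjusted contrast would gain precision at almost no cost

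*Protocol article*

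**What the plan says.** - **Randomised contrast.** Power Analysis and Sample Size Estimation: "The sample size was calculated for the group-by-time interaction, which tests the differences in change over time between the study groups". The calculation counts baseline among three measurements: "with all measurements obtained at baseline and 2 additional measurements over an 8-week period".
- **Baseline data.** Baseline Data Capture: "all participants will undergo baseline data capture using their current passive energy storing and returning prosthesis". A passive-foot value is therefore available for each outcome.
- **Device comparison.** Planned Statistical Analysis for Pain Outcomes lists measures to be "statistically compared between baseline (energy storing and returning condition) and each follow-up visit with the powered ankle-foot prosthesis (weeks 4 and 8" and, like the biomechanical section, sets passive against powered within participants.
- **Adjustment.** Statistical Analysis refers to control variables without listing them. Limitations gives examples: "the statistical analysis models will also adjust for specific parameters (eg, age, time since limb loss, and etiology of limb loss", and adds knee type. The baseline value of the outcome is not among them.
- **Cognitive models.** These list ankle-foot type, PT and participant. How PT is coded at the baseline visit is not said.

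**The concern.** Both arms are measured on the passive foot before either starts on the powered device, so under randomisation they differ at baseline only by chance. A group-by-time test that gives each arm its own baseline mean yields, at each follow-up visit, a difference in change scores. That subtracts the whole chance baseline difference, although only a fraction rho of it is expected to persist. Regressing on the baseline value, or using one baseline mean for both arms, removes only the expected part and leaves less noise.

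With 15 per arm, chance imbalance is not small, and the same participants would support a tighter estimate of the PT effect. What is at stake is precision and power, not bias.

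**Working it through.** **Inputs.** From the article: "30 participants, 15 (50%) in each group"; "Assuming an α error rate of 5"% (sidedness not stated, two-sided assumed); and the Table 5 differences and SDs, "obtained from preliminary analyses". Not given: rho, and whether the SDs are of raw values or of change.

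**1. The plan's own powers.** Standardised differences (difference/SD) in Table 5 order are 0.03/0.04 = 0.75, 15/26.9 = 0.558, 1.1/1.2 = 0.917, 60/61 = 0.984 and 8.4/8.8 = 0.955.
- SDs read as SDs of change, two-sample t test, 15 per arm: power 51, 31, 68, 74 and 71%. The article states 85, 82, 98, 96 and 96%, so this reading does not reproduce them.
- SDs read as raw SDs, so that the SD of change is SD × sqrt(2(1−rho)): the stated powers need rho = 0.78, 0.87, 0.82, 0.76 and 0.77. With the interaction F test, a constant effect at both follow-ups and compound symmetry, they need 0.76, 0.85, 0.79, 0.72 and 0.74. The implied range is about 0.72 to 0.87.

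**2. Variance per participant, one follow-up visit, equal variance s² at both visits.**
- Change score: 2s²(1−rho)
- Baseline-adjusted: s²(1−rho²)
- Ratio: (1−rho)(1+rho) / [2(1−rho)] = (1+rho)/2

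Estimating the slope with 30 participants multiplies the adjusted variance by about 1 + 1/26 = 1.038.

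| rho | ratio | loss | net ratio (×27/26) | net loss |
|---|---|---|---|---|
| 0.3 | 0.650 | 35% | 0.675 | 32.5% |
| 0.5 | 0.750 | 25% | 0.779 | 22% |
| 0.7 | 0.850 | 15% | 0.883 | 12% |
| 0.72 | 0.860 | 14% | 0.893 | 11% |
| 0.87 | 0.935 | 6.5% | 0.971 | 3% |
| 0.9 | 0.950 | 5% | 0.987 | 1.3% |

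In participants, 30 analysed on change carry the information of 22.5 analysed with adjustment at rho 0.5 (30 × 0.75), and of 25.5 at rho 0.7, before the slope cost.

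**3. Simulation.** With 40,000 trials and 15 per arm, the adjusted/change ratio was 0.785 at rho 0.5 and 0.881 at 0.7, in line with the net column. A model that keeps baseline as a response but gives both arms one baseline mean had ratios of 0.757 and 0.850 (rho treated as known).

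**4. Mean of weeks 4 and 8, compound symmetry.** The change variance is 1.5s²(1−rho) and the adjusted variance is s²[(1+rho)/2 − rho²], giving a ratio of (1+2rho)/3. The loss is 33% at rho 0.5 and 20% at 0.7, before the slope cost.

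**5. Chance imbalance.** The standard error of the baseline mean difference is sqrt(2/15) = 0.37 SD. Given an imbalance of that size, a change contrast is displaced by (1−rho) times it: 0.18 SD at rho 0.5 and 0.11 SD at 0.7. Over all randomisations this averages to zero.

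**6. Power, illustration only.** If the 6MWT SD is an SD of change, power is 74% on change. Adjusted, it is about 85% at rho 0.5 and 81% at 0.7 before the slope cost; a simulation gave 84% and 79%. On this reading the stated 96% is not reproduced, and that is a separate matter from baseline adjustment.

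**The case against.** The strongest reply is that the defect is inferred. The sentence on group-by-time describes the sample-size calculation. No analysis section writes that model out or says that the arms have free baseline means. The control variables are left open, the example list is not exhaustive, and a condensed article may leave covariates to a full protocol or SAP that is not shown. A reader might infer that the plan rules out baseline adjustment; the text does not support that. What stands against the reply is that the one randomised contrast the article defines is a difference in change, and nothing stated modifies it.

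Three other strong readings also fail:
- **That keeping baseline among the responses causes the loss.** It does not. A common-baseline model keeps it there and loses almost nothing. If PT is coded as absent for everyone at baseline, the listed cognitive-model terms already form such a model.
- **That the baseline-versus-follow-up comparisons show the same fault.** They address powered versus passive within participants, where baseline must be a response.
- **That 15 to 25% is an established loss.** It rests on an assumed rho of 0.7 to 0.5. Table 5 read with raw SDs points to a higher rho and a smaller loss.

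It is also fair that a change contrast is unbiased under randomisation and in common use.

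**Conclusion.** The point holds as an efficiency improvement. The article defines the randomised PT contrast as a difference in change and states no baseline adjustment or common baseline mean. If the arm means are free at baseline, the single-visit loss is about 12 to 22% net at rho 0.7 to 0.5, and roughly 3 to 11% net at the rho implied by Table 5 with raw SDs. These figures assume equal variances at baseline and follow-up, a continuous outcome and a two-sided 5% test. They do not apply to ordinal outcomes assigned to the Friedman test. The change contrast is not biased and the trial is not invalid on this account. The change is still worth making because the baseline data are already collected and the sample is small.

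**What to change.** In Statistical Analysis and in Power Analysis and Sample Size Estimation, state for continuous outcomes that the PT effect is tested at weeks 4 and 8 by one of:
- a mixed model for the two follow-up values with the participant's own passive-foot baseline value as a covariate, taken at the same walking speed for gait outcomes; or
- a constrained longitudinal model for all three visits, with one baseline mean common to both arms and arm-by-follow-up-visit terms.

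Keep powered versus passive as a within-participant contrast. State the assumed rho and whether the Table 5 SDs are raw or of change, and show the gain over a range of rho.

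Study Overview places randomisation after baseline testing and device fitting, whereas Informed Consent, Enrollment, and Randomization places it directly after consent. Reconcile the two, and use the covariate form if allocation could have been known at baseline testing.

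The cost is a wording change and one degree of freedom per outcome, with no new data.

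### Table 5's powers for the group-by-time test do not follow from its printed differences and SDs, and the ground reaction force rate row fits no assumption that fits the other rows

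*Protocol article*

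**What the plan says.** The section Power Analysis and Sample Size Estimation names the target of the calculation: "The sample size was calculated for the group-by-time interaction, which tests the differences in change over time between the study groups". The design behind it has "all measurements obtained at baseline and 2 additional measurements over an 8-week period", and alpha is 5% with sidedness not stated. The article adds that "Table 5 presents the power achieved for each measurement for 30 participants, 15 (50%) in each group". The measures entering the calculation were "obtained from preliminary analyses".

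The middle column of Table 5 is headed "Difference, mean (SD", with the bracket closed after it. Its entries are 0.03 (0.04) J/kg for leading limb work, 15 (26.9) N/kg/s for ground reaction force rate, 1.1 (1.2) N m/kg/s for knee adduction moment rate, 60 (61) m for the 6-minute walk test (6MWT) and 8.4 (8.8) for PEQ utility. The stated powers are 85, 82, 98, 96 and 96%. The section does not say whether the SD belongs to a change or to a single visit, and it gives no within-participant correlation.

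**The concern.** All participants receive the powered device, so randomisation addresses one question only: whether device-specific physical therapy adds to it. The group-by-time interaction is the test of that question, and Table 5 is the article's only justification of 30 participants for it.

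The standardised differences in the table run from 0.56 to 0.98. With 15 per arm, differences of that size do not ordinarily give 82 to 98% power for a between-group comparison. The rows also sit oddly together: ground reaction force rate at 0.56 SD has 82%, almost the same as leading limb work at 0.75 SD with 85%. If the powers are too high, the trial is presented as more able to answer its randomised question than its own inputs show.

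**Working it through.** Rows are always in the order leading limb work / ground reaction force rate / knee adduction moment rate / 6MWT / PEQ utility. All inputs are from Table 5 and the text above it. A two-sided test is my assumption.

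**1. SD read as the SD of change.** With d = difference / SD and n = 15 per arm, the noncentrality is λ = d × √(15/2). Power is the probability that a noncentral t with 28 df exceeds 2.048.

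| Row | d | λ | Power | Stated |
|---|---|---|---|---|
| Leading limb work | 0.03/0.04 = 0.750 | 2.05 | 51% | 85% |
| Ground reaction force rate | 15/26.9 = 0.558 | 1.53 | 31% | 82% |
| Knee adduction moment rate | 1.1/1.2 = 0.917 | 2.51 | 68% | 98% |
| 6MWT | 60/61 = 0.984 | 2.69 | 74% | 96% |
| PEQ utility | 8.4/8.8 = 0.955 | 2.61 | 71% | 96% |

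On this reading the stated powers would need 33 / 55 / 40 / 30 / 32 per arm.

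**2. Can this reading be rescued?**
- Rounding: taking the largest difference and smallest SD that round to the printed entries gives at most 75 / 33 / 75 / 75 / 72%.
- One-sided 5%: 64 / 44 / 79 / 84 / 82%.
- Three-visit interaction F test, full divergence at both follow-ups: 53 / 32 / 72 / 78 / 75%.
- Mean of both follow-ups against baseline, compound symmetry: 63 / 40 / 80 / 85 / 83%.

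Every row stays below its stated power in all four.

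**3. Other sample-size readings.**
- 30 per group instead of 30 in total: 82 / 57 / 94 / 96 / 95%. Force rate fails by 25 points.
- Paired test on all 30: 98 / 84 / 99.8 / 99.9 / 99.9%. Only force rate comes within 2 points, and this is a within-participant test, not a comparison of groups.

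**4. SD read as a cross-sectional SD, σ, with visit-to-visit correlation ρ.** The mean of two follow-ups minus baseline has variance σ²[(1+ρ)/2 + 1 − 2ρ] = 1.5σ²(1−ρ) under compound symmetry. At ρ = 0.7 this is 0.45σ², an SD of 0.671σ, so λ = d × √7.5 / 0.671 = 3.06 / 2.28 / 3.74 / 4.02 / 3.90. Power is 84 / 59 / 95 / 97 / 96% against the stated 85 / 82 / 98 / 96 / 96%. Four rows agree within about 3 points. Force rate is 23 points short, and rounding of its entries (d from 0.538 to 0.577) moves it only between 56 and 62%.

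The correlation that each row needs is 0.71 / 0.82 / 0.76 / 0.67 / 0.69. Setting ρ = 0.82 throughout to suit force rate gives 97% for leading limb work, against 85%. With a single follow-up, variance 2σ²(1−ρ), the needed correlations are 0.78 / 0.87 / 0.82 / 0.76 / 0.77. A search for one common multiplier of d (λ = k × d), allowing for rounding of the entries, never matched more than four rows.

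**The case against.** The column heading does not say that the SD is the SD of change. A difference with the measure's ordinary SD, plus a within-participant correlation, is a normal input to repeated-measures power software. The preliminary analyses covered five different measures, so the correlations may well differ by measure. A journal article may leave correlation, sidedness and software settings to the full protocol. Baseline adjustment of the two-visit mean would lower the correlations needed to 0.60 / 0.80 / 0.70 / 0.52 / 0.57. And the first objective is powered against passive, where a paired test on all 30 has 84% or more on the same figures.

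Much of this stands. A reader might infer that the trial's true power is 31 to 74%. The documents do not support that for the whole table, because those values hold only if the SDs are SDs of change, and four rows are close to what an ordinary correlation of 0.7 would give. A reader might also take the order of knee adduction moment rate (0.92 SD, 98%) and 6MWT (0.98 SD, 96%) as an error, but rounding of 1.1 (1.2) could account for it. Nor does any passage say how a null between-group result will be read, so a forecast of misreading is conjecture. The absence of a correlation from an article is not in itself a fault.

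What does not stand is the defence of the force-rate row. Under each set of common assumptions tried that fits the others, it falls well short. The power of the paired device comparison is beside the point, since the article says the calculation was for the difference in change between groups.

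**Conclusion.** The point holds in limited form: the printed differences and SDs do not give the printed powers for the named test at 15 per arm. The size of the discrepancy depends on what the SD is. If it is the SD of change, each row is overstated, by 22 to 51 points (96 − 74 for 6MWT, 82 − 31 for force rate). If it is cross-sectional, four rows are roughly right at an unprinted correlation of about 0.7, and force rate is about 59% instead of 82%.

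Force rate is the firm part. Its 82% requires a correlation of about 0.82 particular to that measure, or it comes from a paired powered-versus-passive calculation (84%), which does not address the randomised contrast. The article does not show which. These results assume a two-sided 5% test, 15 complete participants per arm and, for the two-follow-up calculations, compound symmetry.

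**What to change.** Keep N=30 and restate Table 5.

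- For each row, give the contrast, the type of SD, the visit-to-visit correlation and the test. The protocol does not designate week 4 or week 8 as the decisive visit, so the table should name the contrast that was actually used and not introduce one.
- Recompute the power column for the between-group difference in change. If the SDs are SDs of change, print 51 / 31 / 68 / 74 / 71%. If they are cross-sectional, print the correlations so that the figures can be reproduced.
- Correct the ground reaction force rate row in any case. 82% could remain only beside a documented correlation of about 0.82 for that measure. If the figure came from a paired calculation, it should be replaced by the between-group value.
- Add the difference detectable with 80% power at 15 per arm, which is 1.06 SD of change. If the table's SDs are of that kind, this is about 65 m for 6MWT (1.06 × 61) and about 28.5 N/kg/s for force rate (1.06 × 26.9).

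The cost is the rewording of one table and its lead-in. No participants are added and no study procedure changes. The downside is that the stated power becomes less favourable.
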